#### 13.6.2 BASELINE DESCRIPTIVE STATISTICS

Demographic characteristics and other baseline data of participants enrolled will be tabulated by study group and for overall age and by age strata. Continuous variables (*i.e.*, age, height and weight) and categorical variables (*i.e.*, sex) will be summarized by standard descriptive statistics.

---

#### 13.6.3 PRIMARY IMMUNOGENICITY ENDPOINT ANALYSIS

The primary immunogenicity endpoint will be measured as seroconversion rate (the proportion of participants with at least 4-fold rise vibriocidal titers against *Vibrio cholerae* O1 Inaba and O1 Ogawa compared prior to dosing (Day 0)) of OCV-S (Group C) and Shanchol™ (Group D) after 2 weeks of second dose. The primary immunogenicity endpoint analysis will be done by generalized linear model adjusting for stratification and any imbalances in baseline characteristics. The two-sided 95% CI of seroconversion rate for each vaccine group and the difference will be provided an estimate and non-inferiority of OCV-S will be confirmed if the lower limit of the two-sided 95% CI of the difference of seroconversion rate of OCV-S (Group C) and Shanchol™ (Group D) is greater than the pre-defined non-inferiority margin of -10%.

Primary immunogenicity endpoint analysis will be conducted on the participants in the PPS and FAS.

---

#### 13.6.4 PRIMARY SAFETY ENDPOINTS ANALYSIS

The primary safety endpoint analyses are safety analyses of treatment emergent adverse events (TEAEs). TEAEs are defined for this trial as any AEs/ SAEs that occur on or after Day 0 following OCV-S or Shanchol™ administration. All TEAEs will be summarized by frequency, percentage and associated 95% confidence interval. The frequencies will also be presented separately by dose and will be depicted by system order class and preferred term. Additional frequencies will be presented with respect to maximum severity and relationship to investigational product. All serious TEAEs will also be summarized as above. Serious TEAEs will be presented in listings.

---

#### 13.6.5 SECONDARY ENDPOINTS ANALYSIS

GMT of vibriocidal antibodies against *Vibrio cholerae* O1 Inaba and O1 Ogawa at 2 weeks post second dose will be calculated by vaccine group and for all ages and by age strata. The two-sided 95% CI of GMT and ratio of GMTs will be provided. The non-inferiority of OCV-S will be confirmed if the lower limit of two-tailed 95% CI of the ratio of GMT of OCV-S (Group C) to Shanchol™ (Group D) is greater than the non-inferiority margin of 0.67.

Seroconversion rate of vibriocidal antibodies against *Vibrio cholerae* O1 Inaba and O1 Ogawa at 2 weeks post second dose will be calculated by vaccine group by age strata. The two-sided 95% CI of seroconversion rate and difference of seroconversion rates will be provided. The non-inferiority of OCV-S will be confirmed if the lower limit of the two-sided 95% CI of the difference of seroconversion rate of OCV-S (Group C) and Shanchol™ (Group D) is greater than the pre-defined non-inferiority margin of -10%.

To assess lot consistency, three equivalence tests (Group A vs B, A vs C, B vs C) on GMT of vibriocidal antibody responses against *Vibrio cholerae* O1 Inaba and O1 Ogawa at 2 weeks after second dose of 3 lots of OCV-S will be performed with two-sided significance level of 0.05. The equivalence of GMT at 2 weeks after second dose of two lots of OCV-S will be analyzed using the analysis of variance (or covariance if necessary) model after log transformation. The equivalence of two lots will be confirmed if both limits of the two-sided 95% confidence interval of the ratio of the GMT between two lots of OCV-S is within the equivalence margin of [0.5, 2.0].

Secondary immunogenicity endpoints analysis will be conducted on the participants in the PPS and FAS.

---

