## 13.2 SAMPLE SIZE

The sample size of the study is calculated to provide about 90% power to show primary Immunogenicity objective of immune non-inferiority of OCV-S to Shanchol™ and secondary immunogenicity objective of immune equivalence of three lots of OCV-S of the study and increased to satisfy total safety population of about N=2,530. The given sample size of N=935 participants per OCV-S and Comparator vaccine group in all ages would provide 99% power to detect the non-inferiority of immunogenicity of OCV-S group (Group C) compared to Shanchol™ (Group D) in terms of seroconversion rate. The assumed seroconversion rate of Shanchol™ is 71% for all ages which is considered in the assumption based on the clinical studies conducted in a neighboring country to Nepal (i.e., India). The sample size of N=330, 360, and 245 participants per OCV-S and Shanchol™ would provide 80% power to detect non-inferiority of OCV-S in terms of seroconversion rates of 75%, 71%, and 84% in adults, adolescents, and young children, respectively. The assumed non-inferiority margin is -10% based on WHO TRS 924. One sided test of non-inferiority is used with significance level of 0.025.

The sample size of N=330 per lot of OCV-S in adults will also provide >90% power for three equivalence tests of GMT ratio of immunogenicity among three lots of OCV-S (A vs. B, B vs. C and C vs. A) with overall two-sided significance level of 0.05. Each of two-sided equivalence test have >90% power to show the equivalence of GMT of immunogenicity of OCV-S with two-sided significance level of 0.05. The equivalence margin of ratio was assumed as [0.5, 2.0] according to precedent study of OCV (i.e., Euvichol®) and other oral vaccine trials, the true GMT ratio is assumed as 1 and the coefficient of variation on titer of immunogenicity is assumed as 2.0. The coefficient of variation of GMT of OCV-S was assumed conservatively based on OCV immunogenicity data. In both sample size calculations, 10% drop out rate is assumed conservatively considering the potential large variation of experience between sites.

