| [95% CI]                          |                    |                    |                    | 1.14
[-3.73, 6.01] d,g  | 0.6467 i,g |                    |                    |                    | -1.92
[-5.82, 1.98] d,g | 0.3342 i,g |

Abbreviations: CI=confidence interval; GMT=geometric mean titers; N=number of participants in per-protocol analysis set with non-missing results.

- a The GMT ratio and its 95% CI were calculated as the antilogarithmic of the difference between the mean of the log-transformed data in the test arm and that in the comparator arm with baseline titer adjustment (covariates) in a generalized linear model. Equivalence of GMT ratio between lots of Euvichol-S is confirmed using margin of [0.5, 2.0].
- b The estimated seroconversion rate, 95% CI, and p-values were derived using the generalized linear model (link=identity) for binomial distribution with treatment group as covariate by adjustment for baseline titers. Equivalence of seroconversion rate between lots of Euvichol-S is confirmed using margin of [-10%, 10%].
- c Comparison=GMTGroup C/GMTGroup D
- d Comparison=Group C – Group D
- e Comparisons between Groups A and B
- f Comparisons between Groups A and C
- g Comparisons between Groups B and C
- h The p-value was testing of no significant difference (fold difference=1) in GMT values across the treatment groups using generalized linear model.
- i The p-value was testing of no significant difference (difference=0%) in seroconversion rate across the treatment groups using generalized linear model (link=identity).
- j Comparison across Groups A, B, and C

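### Protocol section 13.6.5 specifies no baseline-titre or age-stratum adjustment for the OCV-S/Shanchol GMT ratios and leaves the lot model open; one pre-specified ANCOVA would be a free improvement

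*Protocol*

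**What the plan says.** Section 13.6.5 of the protocol says that the GMTs two weeks after the second dose "will be calculated by vaccine group and for all ages and by age strata", and then "The two-sided 95% CI of GMT and ratio of GMTs will be provided". Non-inferiority holds if the lower limit of the 95% interval for the Group C to Group D ratio "is greater than the non-inferiority margin of 0.67". No model and no covariate are named.

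The lot comparison, in the same section, "will be analyzed using the analysis of variance (or covariance if necessary) model after log transformation". The text does not say what would make covariance necessary, which covariate would enter, or who decides.

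Four other places bear on this:
- Section 13.6.1 gives a two-sample t-test or ANOVA as the general method for continuous variables.
- Section 13.6.3 writes adjustment for stratification and baseline imbalance into the primary seroconversion model.
- Section 8.4 stratifies randomisation by the three age strata, and the Day 0 visit includes a blood sample before vaccination.
- The results appended to the protocol describe the lot GMT ratios as calculated "with baseline titer adjustment (covariates) in a generalized linear model" (Table S3, footnote a). The caption of Figure S1 calls the Euvichol-S/Shanchol ratio adjusted.

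**The concern.** The GMT ratios decide formal secondary tests: non-inferiority against 0.67 for all ages and in each stratum, and lot equivalence within 0.5 to 2.0. The protocol writes adjustment into the primary model but not into these tests, where the general default is unadjusted. Baseline vibriocidal titres vary widely in this endemic population, so two randomised arms can differ noticeably at Day 0 by chance. An unadjusted ratio carries part of that difference forward and has a wider interval than the data allow.

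For the lots the issue is different. The wording allows either of two models, and the choice could be made after the data are seen.

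**Working it through.** **Inputs.** Section 13.2 states "the true GMT ratio is assumed as 1 and the coefficient of variation on titer of immunogenicity is assumed as 2.0", a 10% dropout rate, and for the lots "The sample size of N=330 per lot of OCV-S in adults will also provide >90% power". After dropout there are about 297 adults, 324 aged 6-17 and 220 aged 1-5 per group, and 841 per group for all ages. The correlation r between log Day 0 and log Day 28 titre is not given; I assume 0.3 to 0.5.

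**1. The plan's own lot figure.** A CV of 2.0 gives SD(ln) = sqrt(ln(1 + 2²)) = 1.269. With 297 per lot, SE = 1.269 × sqrt(2/297) = 0.104. For two one-sided tests, ln 2/0.104 − 1.96 is about 4.7, so power exceeds 99.9%. The stated >90% is reproduced with much to spare, without any adjustment.

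**2. GMT non-inferiority.** The protocol states no power for these tests. Power = Φ(|ln 0.67| / (SD × sqrt(2/n)) − 1.96), with |ln 0.67| = 0.400. ANCOVA replaces SD by SD × sqrt(1 − r²). At SD 1.269:

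| Comparison | n per group | Unadjusted | r = 0.3 | r = 0.5 |
|---|---|---|---|---|
| All ages | 841 | >99.9% | >99.9% | >99.9% |
| 18-40 years | 297 | 97.0% | 98.1% | 99.4% |
| 6-17 years | 324 | 98.0% | 98.8% | 99.6% |
| 1-5 years | 220 | 91.2% | 93.5% | 96.9% |

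The CV of 2.0 is given for the adult lot tests; applying it to children and to all ages is my assumption. If the SD were 2.0, all-ages power would still be 98.4% unadjusted.

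**3. Interval width.** sqrt(1 − 0.3²) = 0.954 and sqrt(1 − 0.5²) = 0.866, so intervals narrow by 4.6% to 13.4%.

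**4. If titres vary more than planned.** SD = ln(upper/lower)/3.92 × sqrt(n). The Day 28 Inaba interval for Group A in Table S3 (560.72 to 792.62, n = 308) gives 1.55. Moving this adult value to ages 1-5 is an assumption. With 220 per group, power is 77%. What that 77% represents depends on the reading of Table S3:
- If 1.55 is unadjusted, ANCOVA raises power to 81% (r = 0.3) or 88% (r = 0.5).
- If 1.55 is already baseline-adjusted, as footnote a suggests, the unadjusted SD is 1.55/sqrt(1 − r²). Unadjusted power is then 73% (r = 0.3) or 65% (r = 0.5).

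**5. Chance imbalance at Day 0.** The same formula applied to the Group A baseline intervals gives 2.47 (Inaba) and 2.57 (Ogawa), so about 2.5. The 95% chance range of the baseline GMT ratio is exp(±1.96 × 2.5 × sqrt(2/n)):
- 297 per arm: 0.669 to 1.495.
- 220 per arm: 0.627 to 1.596, again using the adult SD.

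The largest baseline ratio in Table S3 is Ogawa A/B, 1.49 [0.99, 2.23]. With an assumed regression slope of 0.1 to 0.4, such an imbalance moves an unadjusted Day 28 ratio by a factor of 1.49^0.1 = 1.04 to 1.49^0.4 = 1.17. That is small against 0.5 to 2.0, but not negligible against 0.67 in a single stratum.

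**The case against.** The best counter-argument is that section 13.6.5 is silent rather than wrong. It does not call the ratio unadjusted, covariates for secondary endpoints are commonly left to the SAP, and the appended results are adjusted. This stands against any claim that the plan excludes baseline titre or age. It does not remove the point: the section 13.6.1 default points to an unadjusted test, and the conditional lot wording is a statement, not a silence.

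A reader might also infer the following, which the documents do not support:
- *That the analyst may choose between two ratios against 0.67.* The conditional wording occurs only in the lot paragraph, with margin 0.5 to 2.0.
- *That the choice could change the lot result.* Even at SD 1.55/sqrt(0.75) = 1.79 and 297 per lot, power is about 99.4%. All six Day 28 lot intervals in Table S3 lie within 0.68 to 1.44.
- *That stratified randomisation is ignored throughout.* By-stratum tests are within stratum and the lots are adults only. Age could be omitted only from the all-ages ratio, where Groups C and D have equal planned size in every stratum (330, 360, 245).
- *That power at ages 1-5 is 65 to 73%.* This needs an adult SD applied to children, one reading of Table S3 and an assumed correlation.
- *That the unadjusted test is invalid.* Chance imbalance neither biases a randomised comparison on average nor inflates type I error.

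**Conclusion.** The point holds as a free improvement in method; no stated figure is wrong. The protocol specifies no baseline-titre or stratum term for the GMT non-inferiority ratios and does not fix the lot model, although the data needed are collected from everyone.

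The benefit is moderate: somewhat narrower intervals, no carry-over of chance Day 0 imbalance, and a lot model settled in advance. It counts most for the by-stratum tests against 0.67. At ages 1-5, unadjusted power is about 91% at the protocol's CV and falls if variability is larger. The sizes rest on the assumed correlation and slope and on adult variability applied to other ages. The lot and all-ages conclusions are safe either way.

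**What to change.** In section 13.6.5, specify one ANCOVA on log Day 28 titre for every GMT comparison. Its terms are vaccine group (or lot) and log Day 0 titre of the same serotype, plus age stratum in the all-ages comparison only. Take the ratio and its 95% interval from this model for the tests against 0.67 and against 0.5 to 2.0. Delete the words *if necessary* from the lot paragraph, and show unadjusted GMTs descriptively.

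A site term is optional and not part of this change, since randomisation is stratified by age alone. The cost is wording in the protocol, repeated in the SAP. No new samples or assays are needed. A participant without a Day 0 titre cannot enter the model, but cannot be assessed for seroconversion either.

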#### 13.6.6 ADHERENCE AND RETENTION ANALYSES

Summaries of Participants Disposition will be based on safety analysis set (SAF). A flow diagram of participant disposition (CONSORT flow diagram) will illustrate the progress of participants through the study duration from initial screening for eligibility to the completion of the primary outcome assessment. Number and percentage by vaccine group will be given for participants in the FAS and PP analysis sets, and reasons for study discontinuation.

---

#### 13.6.7 PLANNED INTERIM ANALYSIS

No interim analysis is performed.

---

#### 13.6.8 ADDITIONAL SUB-GROUP ANALYSIS

The immunogenicity analyses will be repeated by age strata. A potential difference in safety and immunogenicity by 'sex' and 'age strata' may be investigated.

---

#### 13.6.9 MULTIPLE COMPARISON/MULTIPLICITY

No multiplicity adjustment is taken relative to non-inferiority and lot consistency tests.

---

#### 13.6.10 EXPLORATORY ANALYSES

Seroconversion rate of vibriocidal antibody responses against *Vibrio cholerae* O1 Inaba and O1 Ogawa at 2 weeks post second dose of will be calculated by OCV-S (Group A, B, and C in adults) vaccine group. The two-sided 95% CI of seroconversion rate and difference of seroconversion rates will be provided.

Seroconversion rate and GMT of vibriocidal antibody responses at 2 weeks after first dose of OCV-S or Shanchol™ titers against *Vibrio cholerae* O1 Inaba and O1 Ogawa will be calculated. The two-sided 95% CI of seroconversion rate and the difference of seroconversion rates and GMT and ratio of GMTs will be provided by vaccine group for all ages and by age strata.

## 14. SOURCE DOCUMENTS AND ACCESS TO SOURCE DOCUMENTS

Data recorded on the electronic Case Report Forms (eCRF) will be verified by checking the eCRF entries against source documents (i.e., all original records, medical records, diary cards, memory aids, etc.) in order to ensure data completeness and accuracy as required by study protocol. Source documents will be stored at the clinical site in a secured place under lock and key. The investigator and/or site staff must make eCRFs and source documents of participants enrolled in this study available for inspection by IVI clinical team, clinical research associate (CRA) or its representative at the time of each monitoring visit.

At a minimum, source documentation must be available to substantiate participant identification, eligibility and participation, proper informed consent procedures, dates of visits, adherence to protocol procedures, adequate reporting and follow-up of adverse events, administration of concomitant medication, study vaccine receipt/dispensing/return records, study vaccine administration information, and date of completion and reason. Specific items required as source documents will be reviewed with the investigators before the study.

The source documents must also be available for inspection, verification and copying, as required by regulations, by officials of the regulatory health authorities (e.g., NRAs, others) and/or site IRB/IECs and for possible audit by IVI Quality Management, Regulatory agency, notified body and collaborators/donors. The investigator and study site staff must comply with applicable privacy, data protection and medical confidentiality laws for use and disclosure of information related to the study and enrolled participants.

The participant must also allow access to medical records. Each participant should be informed of this prior to the start of the study by administration of the informed consent process per ICH E6 (R2).

Each participant will have a complete source documentation of records including study logbooks, ICF, lab reports and test results for the entire study period. Appropriate source documents will be prepared by study staffs. These records must be available to the IVI and regulatory authorities upon request for review.

## 15. DATA HANDLING AND RECORD KEEPING

### 15.1 DATA COLLECTION AND MANAGEMENT RESPONSIBILITIES

Electronic Case Report Forms (eCRF) will be used for recording data for each participant enrolled in the study. The site investigators are responsible to ensure the accuracy, completeness, legibility and timeliness of the data captured in eCRF. Data captured in the eCRF derived from source documents and should remain consistent with those source documents. In case of discrepancies, data will be clarified and corrected. IVI will provide guidance to investigator on making corrections to the eCRF.

Study staff will extract all data collected in source documents and workbooks for computerization into the eCRF. Data will be entered into the electronic Case Report Form (CRF) Data will be entered into eCRFs designed on EDC system which is in compliance with industry regulations such as the FDA's 21 CFR Part 11, EMA Annex 11, GAMP5, etc. The entire data collection and handling will be monitored through the implementation of individual credentials to maintain appropriate database access and ensure database integrity. Edit checks will be programmed in the EDC system to identify data entry errors during transcription, including range and consistency checks wherever applicable.

All sequential changes made will be captured in the audit trail in the EDC system which will also provide error reports and summary reports for each activity. Data entry and cleaning will be conducted at the sites. Final data cleaning and data locking will be reviewed by IVI, and data analysis will be performed at the IVI. Unblinding of study groups will be carried out after database lock. All data will be stored in a secure data base maintained by EDC system.

### 15.2 STUDY RECORDS RETENTION

The site Principal Investigators (PI) will retain all study records that support eCRFs for this study (i.e., ICFs, source documents, IP dispensing records) required by sponsor and by the applicable regulations in a secure and safe facility. The PI will consult IVI representative before disposal of any study records and will notify the sponsor of any change in the location, disposition, or custody of the study files. These documents should be retained for not less than 3 years after the approval of a marketing application or at least 2 years has been elapsed since formal discontinuation of

clinical development of the investigational product. The documents will be stored as per NHRC guidelines.

If a PI retires, relocates or for other reasons withdraws from the responsibility of keeping the study records, custody must be transferred to a qualified person who will accept this responsibility. The Sponsor must be notified in writing of the name and address of the new custodian. The PI will be responsible for retaining sufficient information about each participant, *i.e.*, name, address, telephone number, and participant identifier in the study, so that the sponsor and/or other regulatory authorities may have access to this information should the need arise.

If site expresses its inability to retain those study documents beyond certain period due to space constraints or due to an unanticipated event, then IVI will take the help of external archiving vendor.

### 15.3 PUBLICATION AND DATA SHARING POLICY

IVI assures that the key design elements of this protocol will be posted in a publicly accessible database such as Clinicaltrials.gov. All data collected during this study will be used to support this vaccine development plan until licensure and WHO prequalification. All individual data will stay strictly confidential. Analyzed data may be presented in scientific conferences and published in peer-reviewed scientific journals. Anyone wishing to publish or present site-specific data obtained during and/or after completion of the study will conform to study site and IVI data sharing policies and then forward the publication and/or presentation for review and approval to IVI and manufacturer.

## 16. ETHICS/PROTECTION OF HUMAN PARTICIPANTS

### 16.1 REGULATORY AND ETHICAL COMPLIANCE

The investigators will ensure that this study is conducted in full conformity with the ICH E6 (R2) (Guidelines, Council for International Organizations of Medical Science (CIOMS), local country's ethical policy statement or the Declaration of Helsinki, whichever provides the most protection to human participants.

### 16.2 PARTICIPANT AND DATA CONFIDENTIALITY

Researchers shall adhere to the principles of transparency, legitimate purpose, and proportionality in the collection, retention, and processing of personal information.

Participant confidentiality is strictly held in trust by the participating investigators, their staff, and the sponsor and their agents. This confidentiality is extended to cover testing of biological samples in addition to the clinical information relating to participants. Therefore, the study protocol, documentation, data, and all other information generated will be held in strict confidentiality. No information concerning the study, or the data will be released to any unauthorized third party without prior written approval of the sponsor.

The study monitor, other authorized representatives of the sponsor, representatives of the IRB/IEC or pharmaceutical company supplying study product may inspect all documents and records required to be maintained by the investigator, including but not limited to, medical records (office, clinic, or hospital) and pharmacy records for the participants in this study. The clinical study site will permit access to such records.

The study participant's contact information will be securely stored at clinical site for internal use during the study. At the end of the study, all records will continue to be kept in a secure location for as long a period as dictated by local IRB/IEC and local regulations.

Individual participants and their research data will be identified by a unique study identification number. The study data entry and study management systems used by clinical site and by Data Management will be secured and password protected.

Researchers must respect participants' right to privacy. Unless required by law, the confidentiality of information shall at all times be observed. Records that link individuals to specific information shall not be released. No personal identifier will be used in any publication or communication used to support this research study. The participant's identification number will be used in the event it becomes necessary to identify data specific to a single participant.

